**TUFTS MEDICAL CENTER/TUFTS UNIVERSITY RESEARCH PROTOCOL**

**Version date: 7/21/2017**

**Principal Investigators:** [name] [name] (IRB-PI) and [name]

**Co-Investigator:** [name]

**Study Physician:** [name]

**Study Title:** Worksite Wellness Study

1. **Aim and Hypotheses**

Worksites offer attractive locations for reducing the national prevalence of overweight and obesity. Interventions that are both effective and sustainable in producing long-term changes in health and employee wellness are urgently needed. In an 18-month worksite randomized controlled trial in 12 worksites (defined as whole, moderate sized, worksites or subunits of larger worksites) we propose the testing of two lifestyle approaches that are aimed at behavior modification for achieving long-term improvements in health and quality of life. Worksites randomized to the immediate intervention arm will receive the two wellness programs, and the randomized control sites will participate in outcomes assessments only for the initial 6 month period after which participants will be able to participate in the program of their choice. The multiple-program intervention will be tested against the control in a variety of employment types to determine effectiveness for quality of life, health and weight-related wellness across a broad range of demographics. The study will be officially registered as a clinical trial with the intention of submission to a top medical journal, and will be referred to as the Worksite Wellness Study.

The primary focus of the Worksite Wellness Study is to improve health related quality of life, with a particular focus on a decrease in cardiometabolic risk factors, improved weight-related wellness, and improved energy in work and life.

We plan to test our central hypothesis and accomplish the study objective with the following technical objectives:

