1. **Conduct a randomized controlled trial assigning worksites in a 2:1 ratio to a multiple-program health intervention or a wait-listed control.** The multiple-program intervention will be a combination of the Human Performance Institute (HPI) intervention and iDiet, a behavioral weight loss program, with randomization to either partial provided food or a gift card for self-selection of food. Within worksites, employees will be eligible to select either the HPI intervention or the behavioral intervention. **Primary outcomes will be quality of life and energy levels (HPI participants and controls) and weight (weight loss intervention participants) at 6-18 months.** Secondary outcomes include cardiometabolic risk factors.
2. *The HPI working hypothesis* is that enrollment in the HPI intervention will result in significant improvements in quality of life (primary outcome) and energy levels compared to controls over 6 months and no significant decrease in quality of life during the subsequent 12-month period in the intervention participants. Exploratory outcomes also tested will include body weight and fat, fasting blood glucose, a lipid panel and systolic and diastolic blood pressure.
3. *The behavioral weight loss program working hypothesis is that* iDiet participants receiving gift card will lose weight over the first 6 months compared to weight listed controls and will lose weight compared to baseline over 18 months. In addition, iDiet participants receiving the ready-prepared foods will lose more weight over 18 months compared to participants receiving gift cards.
4. An exploratory hypothesis is that greater weight loss will be associated with reduced levels of hunger and food cravings and increased satiety.
5. **Background and Rationale**
   1. Background

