The interventions that are to be used in this study are all long-term group behavioral wellness programs, and implementing them simultaneously allows for a combined evaluation of these programs for concurrent use in the workplace. The combination of the 2 programs is anticipated to be highly acceptable to worksites because they are commercially available for large scale dissemination and delivery in a group format. It is anticipated that both of these programs may be beneficial in affecting wellness..

- 1. Rationale

The rationale for these technical objectives is that there is an urgent need for sustainable worksite wellness interventions generally, and two successful programs designed to achieve worksite wellness and improvements in employee health are being tested for sustainability in this long term study. Preliminary data suggests that HPI may be particularly effective in improving overall energy, as well as general and mental health, while our prototype iDiet intervention may be particularly effective and sustainable for long-term improvements in weight. Furthermore, the provision of foods for a subset of participants in the iDiet arm may facilitate adherence and overall weight control, suggesting that provided foods offer an important adjunct to enhance effectiveness of worksite weight loss programs. By conducting a comparison of the more specific dietary composition profiles in the iDiet to the energy maintenance focus of the HPI intervention we will be evaluating current best practices for an extended period of time (18 months) at worksites. The intention is to help all employees and worksites participating in this research program and to identify the most optimal long term approach to wellness, involving dietary and exercise recommendations as well as particular food provisions necessary for sustainable health. Once the results of this study are available, the most effective long-term approach to health and wellness/weight control can then be used for scaling practical, effective programs for worksite wellness.

1. **Research Plan**

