For the HPI intervention in whom those randomized to intervention will be compared primarily with subjects at control sites who elected the HPI intervention prior to workplace randomization, a mixed linear model with worksite nested within the randomization to HPI intervention or control as a random factor will be use to assess the effect of the intervention on change in vitality scale score. Baseline vitality score, weight, ethnicity and gender will be included as covariates.

The diet intervention will compare those receiving the iDiet with a primary outcome of percent change in weight at 6 and 18 months. To assess the effect of diet and food delivery method, a multi-factor model with diet, food and worksite as independent variables will be used, controlling for baseline weight, gender and ethnicity. Interactions between diet and worksite, food and worksite and food and diet will be assessed and included in the final model if significant. Change in weight for the HPI intervention andchange in vitality score for those in the diet intervention will be included as secondary outcomes.

Secondary analyses will include a comparison of the 3 intervention arms (with and without provided food for the iDiet) as well as the combined effect of intervention on change in anthropometric measures including body fat, and also lipids, blood glucose levels and blood pressure using the same models described above adjusting for the appropriate baseline values. Additionally, regression models will be used to assess the effect of different adherence metrics, activity levels, appetite regulation (hunger and food cravings) and measures of wellbeing on outcome measurements both within and between intervention groups for each arm of the study. In addition, predictors of changes in cardiometabolic parameters will be examined. Prior to enrollment of subjects, a formal data analysis plan will be prepared and submitted as part of clinical trial registration.

1. **Worksite Characteristics**

A convenient sample of worksites in the Greater Boston area, consisting of worksites which have previously expressed interest, and respond to the recruitment letters will be invited to participate in the Worksite Wellness Study. The first twelve eligible worksites with a higher employee interest in worksite wellness will then be invited to enroll in the study.

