Participants will receive up to $75 over the course of the study, for completing the assessments outlined at each time point (Table 1). Participants will receive this amount as $25 for doing all 6 month testing, $25 for doing all of month 12 testing, and $25 for doing all of month 18 testing. These amounts will be prorated and given to participants based on completion of testing at each time point and if participants withdraw, or are withdrawn from the study for any reason. If institutional policy dictates that employees are not allowed to receive such stipends then such policies will override the provision of stipends as stipulated for each time point.

For diet intervention participants randomized to the voucher group, vouchers of $63 will be given at baseline and weeks 4, 8, 12, and 16, 20 the time of food distribution, for a total of $378 in gift card vouchers.

1. **Payment for research-related injury:** Subjects will be encouraged to see their primary care physician, however no monetary compensation for injury will be offered.
2. **Outcomes**

The primary outcomes are a change in measured weight from baseline to 18 months in iDiet participants, and a statistically significant improvement in energy status for HPI participants and baseline to 6 months in comparisons with the controls. Additional outcomes include: cardiometabolic risk factors, quality of life, employee productivity, purpose in life, measured dietary intake and cravings, satiation and satisfaction of food provisions, as well as changes in physical activity. Further outcomes include changes in weight, blood pressure employee energy and productivity in non-participating employees at the intervention worksites. Differences in overall mean values between the intervention participants and controls, as well as overall mean values between interventions will be compared using *t*-tests and proportions will be compared using *χ*2 analyses.

1. **Tissue banking considerations:** There will be no tissue samples taken as part of this study and no tissue banking is planned or anticipated.

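### The aim of testing the randomised two-programme package on quality of life is left to a t-test that ignores worksite randomisation; the planned combined analysis omits that outcome

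*Protocol*

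**What the plan says.** The Aim and Hypotheses section states: "The multiple-program intervention will be tested against the control in a variety of employment types to determine effectiveness for quality of life, health". Under Background and Rationale, one reason for running both programmes together is that "implementing them simultaneously allows for a combined evaluation of these programs for concurrent use in the workplace". What is randomised to the 12 worksites, 2:1, is the package against a wait-list.

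The first technical objective then assigns primary outcomes by programme: "Primary outcomes will be quality of life and energy levels (HPI participants and controls) and weight (weight loss intervention participants) at 6-18 months".

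Sample size and statistical analyses describes three sets of models:

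- A mixed model for change in vitality, with worksite as a random factor. It compares HPI participants mainly with control-site employees who had chosen HPI before worksite randomisation. The covariates are baseline vitality, weight, ethnicity and gender.
- A model for percent weight change in the diet arm, with diet, food and worksite as factors. The same paragraph also covers vitality in this group: "in vitality score for those in the diet intervention will be included as secondary outcomes".
- Secondary analyses that include "the combined effect of intervention on change in anthropometric measures including body fat, and also lipids, blood glucose levels and blood pressure". For these, the earlier models are reused, each with its own baseline value as a covariate.

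The Outcomes section lists quality of life among the additional outcomes. It then says that "Differences in overall mean values between the intervention participants and controls" will be compared by t-test.

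**The concern.** The one modelled analysis that pools both programmes against control leaves out the domain the protocol calls its primary focus. A sponsor following the text would answer the package-level quality-of-life question with the t-test under Outcomes. That test treats 600 employees as independent, although only 12 worksites were randomised. The protocol's own sample-size paragraph says that the variance between worksites has to be counted. A falsely significant package effect on quality of life or energy would be far more likely than the stated 5%.

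The pooled models also have no listed term for the programme each person chose. That choice is recorded at screening, before worksites are randomised, and goes with different lower BMI limits (20 for HPI, 25 for weight loss).

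**Working it through.** **Inputs.** From Sample size and statistical analyses: within-worksite SD 15, between-worksite SD at most 3.4, 20 HPI participants per site, effect 9 points, 12 sites split 8 and 4, two-sided 5%. From Experimental design: about 20 HPI plus 30 iDiet, so 50 per site, giving 400 intervention and 200 control participants.

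**Reproducing the plan's figure (HPI electors, 20 per site).**
- Variance of a site mean = 3.4² + 15²/20 = 11.56 + 11.25 = 22.81.
- SE = √(22.81 × (1/8 + 1/4)) = 2.925.
- Two-sided noncentral t on 12 − 2 = 10 df, 9 points: power 79.2%. The stated 80% is reproduced.

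**Package comparison with clustering (50 per site).**
- Variance of a site mean = 11.56 + 225/50 = 16.06.
- SE = √(16.06 × 0.375) = 2.454.

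**The same comparison by an ordinary t-test.**
- Total SD = √(225 + 11.56) = 15.38.
- SE = 15.38 × √(1/400 + 1/200) = 1.332.
- Check: intraclass correlation = 11.56/236.56 = 0.049; design effect = 1 + 49 × 0.0489 = 3.39; √3.39 = 1.84 = 2.454/1.332.

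**Type I error of the t-test.** 2 × [1 − Φ(1.96 × 1.332/2.454)] = 2 × [1 − Φ(1.064)] = 0.287, about 29%.

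**Sensitivity.** The value 3.4 is an upper limit. At half of it (1.7), the clustered SE is √((2.89 + 4.5) × 0.375) = 1.665 and the naive SE is √227.89 × 0.0866 = 1.307. The type I error is then 2 × [1 − Φ(1.96 × 1.307/1.665)], about 12%. It is 5% only with no variation between worksites.

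**What the clustered package test could show (10 df, SE 2.454).** The detectable average difference at 80% power is 7.6 points. The protocol gives no vitality effect for iDiet, so a range is assumed, with 9 points in HPI and a 40:60 programme mix:

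| iDiet effect | average effect | power |
|---|---|---|
| 0 | 3.6 | 26% |
| 3 | 5.4 | 51% |
| 4.5 | 6.3 | 64% |
| 6 | 7.2 | 75% |
| 9 | 9.0 | 91% |

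**Programme mix, illustration only.** If HPI gained 9 points and iDiet none, a 10-percentage-point change in the HPI share at intervention sites would move the pooled vitality estimate by 0.10 × 9 = 0.9 points. Both figures are assumed, and vitality is not at present in the pooled analysis.

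**The case against.** The aim is introductory and names several domains at once. The technical objectives that follow split the primary outcomes by programme, as do the sample-size and Outcomes sections, and no stated hypothesis calls for a pooled quality-of-life test. This stands: the package comparison is not a primary objective left without an analysis, and it belongs among the secondary analyses.

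A package-level comparison does exist, under Outcomes. This also stands, but that comparison is where the error lies. A t-test on the 12 site means would respect the design; the text speaks of participants and controls and makes no provision for worksite.

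Three stronger readings are tempting, and the document does not support them:

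- A reader might infer that the plan ignores elected programme. The text only lists no such term for the pooled models. It reuses the models described earlier, and the HPI model does match controls on the elected programme. A formal data analysis plan is mentioned and not shown, and it may settle the matter.
- A reader might infer that the 60% of intervention participants in iDiet (30 of 50 per site) never enter a vitality comparison with controls. Vitality is a secondary outcome for them, future iDiet participants at control sites complete the SF-36, and the diet factor in that model is not defined. The text is unclear and does not establish exclusion.
- A reader might take the 0.9-point mix shift as a bias in the planned weight or lipid results. It is not; no such shift has been derived for those outcomes. Programme choice precedes randomisation, so variation in mix arises by chance.

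The possible analysis plan does not remove the main point, because the protocol itself names an unclustered test.

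**Conclusion.** The point holds as a mismatch among three places: the aim, the outcome list of the combined analysis, and the t-test under Outcomes. The package-level quality-of-life comparison rests only on the last of these. At the protocol's upper between-worksite SD, the t-test understates the standard error by a factor of 1.84, and its type I error is about 29% instead of 5%. The 29% assumes 50 people at every site, SDs of 15 and 3.4, and a normal approximation; at half the between-worksite SD it is about 12%. The SDs are those given for vitality. Other SF-36 scales would show the same inflation only with the same intraclass correlation.

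The primary analyses by programme are not affected. A correctly clustered package test has modest power unless iDiet also improves vitality, which is a further reason to keep it secondary.

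**What to change.** In Sample size and statistical analyses, add SF-36 vitality and quality of life at 6 months to the outcomes of the combined intervention-versus-control analysis. Fit it to all participants at the 12 sites with worksite as a random factor, as in the HPI model, and label it secondary. In the Outcomes section, replace the t-test with this model for intervention-versus-control comparisons.

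Include the programme elected at screening as a baseline covariate in the combined models. An arm-by-programme interaction is optional. A covariate alone does not fix the mix to which a pooled effect refers; for that, the interaction is needed, with the arm effect averaged over a stated mix.

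The change takes a few sentences and one more model on data already scheduled. The costs are one more secondary test and confidence intervals that are wider than the t-test would give, but correct.

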**Summary of eligibility requirements for worksites to participate**

1. 300 or more employees from a for-profit or non-profit company and/or government institution (including schools, government agencies).
2. Available address and/or email contact for HR/company representative.
3. After understanding the study purpose, HR/company representative and administration’s willingness to be randomized to control or intervention group, and to host onsite and/or online iDiet weight loss groups and facilitate the implementation of the HPI workshop including allowing the interested employees to participate on the assigned dates.
4. Does not have an active weight loss/wellness intervention program onsite currently or within past 6 months or a pending contract for implementation in the immediate future (defined as weekly behavioral groups run by an outside commercial company for ≥14 weeks per year).
5. Low employee turnover rate (approximately 15%)
6. Company has been in operation for at least 3 years
7. HR/company representative can provide the Tufts team with aggregate demographic information (age range of employees, number of males and females etc.).
8. HR/company representative is willing to sign a consent form agreeing to company participation; also, HR/company representative is willing to complete questionnaire to allow preliminary assessment of eligibility, and then send around information and request employees to complete screening questionnaire (or provide emails to Tufts team to do this).
9. HR/company representative is supportive of the study, anticipating that employee enrollment in the program arms will not be problematic (approximately 50 total employees), and are able post informational flyers and study information for employees around the worksite and send occasional reminder emails to all employees prior to the two health surveys (or provide emails to Tufts team so that they can make these contacts).
10. There is a room available for the Tufts team to lead seminars and groups at times that are convenient to the worksite. Also, a bulletin board available for study flyers, and central location for distribution of study handouts and setting up periodic booth for information.
11. **Subject Characteristics**
    - 1. Inclusion criteria:
         1. Willingness to sign an informed consent form
         2. ≥ 21 years of age
         3. Willingness to provide release from his/her physician before starting the intervention program-a requirement for each of the 3 wellness programs which can be faxed to [name], or emailed to [[contact]](mailto:[contact]) or mailed back to the HNRCA at [name].
         4. Willingness to provide email ID and contact information to the commercial program facilitators to receive program materials and other feedback related to program progress.
         5. Willingness to complete outcome assessments and self-monitoring in order to track intervention effectiveness
         6. BMI ≥ 20 kg/m^2^ and < 50 kg/m^2^ at screening, if participant opts into the HPI arm
         7. BMI ≥ 25 kg/m^2^ and < 50 kg/m^2^ at screening, if participant opts into the weight loss arm
      2. Exclusion criteria:
         1. Employees who are temporary contract workers or employees who work remotely most of the time
         2. < 21 years of age
         3. Participation in a weight loss program or intensive wellbeing program at time of enrollment
         4. Pregnant or lactating (per self-reports, now or intended during study)
         5. Prior weight loss surgery or a medical complication that would prevent full participation
         6. Multiple severe dietary intolerances (e.g. gluten combined with dairy or meat) which would reduce intervention adherence
         7. Non-English speaking
         8. Individuals who have lost > 15 pounds in the past 6 months
         9. mobility limitations (inhibiting the ability to stand on one’s own or get on and off of the scale)
         10. Major diseases including active cancer or cardiovascular disease
         11. BMI < 25 kg/m^2^ or ≥ 50 kg/m^2^ at screening, for those that opt-in to the weight-loss group
         12. BMI <20 kg/m^2^ or ≥ 50 kg/m^2^ at screening, for those that opt-in to the HPI group

For those interested in the weight loss intervention, additional exclusion criteria are as follows:

1. Any condition that influences the ability to absorb food (e.g. inflammatory bowel disease or celiac disease)
2. Very active individuals (> 2 hours/day or >14 hours/week of vigorous activity).

We would like to note that there will be no exclusion of participants based on out of range blood values since the physician’s clearance form will serve as the reference document for inclusion in the study. Extreme values will be flagged and per the study physician’s recommendation participants will be sent a notification to see their primary care provider.

Non – English speaking participants will be excluded from participation as the proposed intervention programs and program related materials have yet to be translated into other languages and have yet to be designed or tested for non – English speaking populations. Furthermore we anticipate that since this is a worksite study most if not all employees will be English speaking

- - 1. Withdraw/Termination criteria: Participants will be withdrawn if they develop a condition that renders them ineligible after they sign consent including the period during which they are actively participating in the study. This includes women who self-report pregnancy, those whose health status changes affecting adherence to the diet, safety concerns for either the participant or the researchers, or outcome assessments (questionnaires) reveal that they have an exclusion criterion that they did not disclose at screening. Participants will be withdrawn from the study if they enroll in any other weight loss/intensive wellness program during the 18 month intervention. Furthermore the PIs with the consultation of the study physician may terminate or temporarily withdraw participants at their discretion if they feel that participant safety is of concern.

Participants may withdraw at any time for any reason. If participants decide that they wish to withdraw they will be provided a prorated stipend based on completion of study outcomes for the time point at which they withdraw and provided a stipend is identified at that time point.

If participants are deemed ineligible or withdraw at any time for any reason, any data collected up until this point in time will be retained throughout the duration of the study. We plan to discard this data 10 years after study completion. Retaining this data is necessary to report CONSORT chart details in any study publication(s).

- In addition as stated in the company agreement, “in the event of low employee participation (less than 50 individuals joining the interventions), Tufts may decide to exclude Company Name from the study” any eligible worksite that enrolls may be withdrawn by the Principal Investigator (s).

1. **Risk/benefit assessment:** This is a randomized controlled study that has minimal risk associated with the research activities for worksite participants.

The major potential risk associated with the study is considered to be breach of confidentiality. To address this, upon entry into the study, a coded study ID will be assigned to the study subject and biological materials and questionnaires to maintain confidentiality within the research setting. The signed consent forms data on paper forms will be kept in a locked file cabinet in the USDA Human Nutrition Research Center. Only the principal investigators and Study Coordinator will have access to the master code linking subject identifiers and their study ID. All investigators at Tufts undergo the required continuing recertification for ethical research by human subjects. Study investigators will see only de-identified data. The reviewing IRB is authorized to see fully identifiable data. Computer files and data collection forms will use the subject ID and will not be linked to protected information. The computers used to enter or store study data will be password protected. All data will be entered into StudyTRAX. Security features of StudyTRAX targets include password protection, restricted access to users based on role in the study, role-based access to features, access audit trails, and hosting services (e.g., firewall, secure sockets layer). Taken together, these features ensure access control, audit control, data integrity, user authentication, and transmission security. The research project will be set up in StudyTRAX using their standard procedure which ensures exported datasets are de-identified as defined in the HIPAA privacy regulation [45 C.F.R. §164.514 (b)(2)]. However, there is always the risk that confidentiality may be lost due to reasons beyond the control of study staff.

1. Physical risk: Minimal risk. Participants may experience some mild bruising or discomfort from the finger prick for the point of care assessments. The discomfort is normal and should dissipate. Excess weight loss may also be a potential risk if individuals continue to practice weight loss beyond the time period of the weight loss support group, but this is not recommended in the program. In addition, bloating, intestinal gas, or diarrhea has occasionally been reported with weight loss interventions as part of a change to a whole grain and higher-fiber diet. Participants in the HPI intervention may experience discomfort, during or following the exercise regimen that is provided as part of the training. Coaches will discontinue participants who report discomfort and it is anticipated that since participants have provided a physician’s clearance any discomfort following these sessions will be minimal and should be addressed with their primary care physician as needed. The Tanita Body Composition Analyzer is a scale with a bio-impedance analysis (BIA) function to measure body composition. To do this the device sends a very small charge through the body. The electric charge may interfere with electronic implanted devices. As a safety precaution, we will weigh participants with pacemakers or other implanted electronic devices using the weight-only feature of the scale. The BIA protocol and the data collection form include a question on use of pacemakers and other implanted electronic devices. Data collectors are instructed to elect the weight only feature to obtain weight for participants with these devices.
2. Psychological risk: The risk may be that no weight will be lost by some participants in the behavioral weight loss arms. Additionally, a potential risk is the discomfort associated with responding to questionnaires that may have sensitive information regarding weight and eating behavior.
3. Social risk: Knowledge of participation may not be completely confidential as there is a risk that coworkers are aware of employees who are enrollees in the wellness intervention programs. However, our experience is that the benefits (co-workers encouraging each other and other social support features) far out weight any potential risk and further we have not observed or have heard reports of negative effects.
4. Economic risk: It is possible that the participant may have to pay for a doctor’s visit if an in-person visit is required to obtain the physician clearance form. A small stipend is provided to cover such incidental expenses. No additional payment will be provided.

No compensation will be provided for missed work time for study activities however this will be planned with employee and management support to minimize/avoid missed work time and will be counted as credit rather than as time off.

For the diet arm of the study, class will only be for one hour during lunch or at another convenient time identified by the participants and facilitated by mutual agreement between the iDiet group leader and management. However, if the participants prefer a concurrent online session then intervention delivery will be provided using the online groups with flexibility for some in person groups. No compensation will be provided for missed work time for these classes. However, time required for study activities will be planned with employee and management support to minimize/avoid the impact of missed work time and will be counted as credit rather than as time off.

For the HPI program, a one-time initial workshop involving two and a half days will be required. No compensation will be provided, however time required for study activities will be planned with employee and management support to minimize/avoid the impact of missed work time and will be counted as credit rather than as time off. Please note that both weekend and weekday times will be offered for sign-up and if a participant absolutely cannot take a weekday off, they will have the option to choose weekend times, such as a Friday afternoon through the weekend.

1. Benefit of participation: The direct benefit is the opportunity of receiving a commercial diet or wellness program free of charge. This study has the potential for improved wellness for the participants in the areas of energy, health and weight related wellness. Furthermore, it is anticipated that findings from these studies will help to advance nutrition research.
2. **Specific methods and techniques used throughout the study**
3. **Laboratory tests:** We will measure fasted lipid panel including triglycerides, HDL, LDL and total cholesterol and glucose using the Alere Cholestech LDX® System which requires 40 microliters of blood. Hb A1c will also be measured using the Siemens DCA Vantage® which requires 1 microliter of blood. Research assistants will obtain capillary blood samples using a lancet. Measurements that are out of range (fasting blood glucose >126 mg/dl, TC >240 mg/dl, Hb A1c ≥6.5%) will be flagged in data given to participants, who will be recommended to follow up with their physician. (please note: as stated earlier physician clearance will be required prior to enrollment for all participants). Breakfast bars will be provided to all participants after overnight fasting blood work.

Laboratory tests will be completed at the worksite by study staff using paper data collection forms and will then be entered into the online, password protected database, using their numerical ID. This form has identifiers because the use of electronic de-identified data forms is not feasible due to the large number of participants moving through the measurement stations which could potentially cause errors in measurement recording if the study ID was the only identifier. These forms will be transported from the study site in a locked briefcase and will be kept in a locked file cabinet at the USDA Human Nutrition Research Center on Aging, as detailed in the confidentiality section below.

1. **Study Procedures**

Anthropometry: The research coordinators will take duplicate fasting measurements of weight in program participants to ±0.1 kg at baseline, 6, 12, and 18 months in all subjects using the Tanita TBF300A, self-calibrating scale with 200kg capacity. Participants will be asked to wear light clothing and no footwear. In addition, height will be measured in duplicate to ±0.1 cm at baseline using a portable stadiometer (Seca 214). Fasted waist and hip circumference will be measured in duplicate to ±0.3 cm at baseline, 6, 12, and 18 months in all subjects according to our standard procedures (Seca 201). Fasted blood pressure will be measured to the nearest 1 mmHg at baseline, 6, 12, and 18 months in all subjects using a validated automated monitor (3 measurements, 5 minutes apart after 5 minutes of quiet sitting, using the OMRON HEM-705CP Digital Blood Pressure Monitor). Measurements that are out of range (systolic BP >160 mmHg, diastolic BP >100 mmHg) will be flagged in data given to participants, who will be recommended to follow up with their physician (please note: as stated earlier physician clearance will be required prior to enrollment for all participants).

Anthropometric measurements will be completed at the worksite by study staff using paper data collection forms and will then be entered into the online, password protected database, using their numerical ID. This form has identifiers because the use of electronic de-identified data forms is not feasible due to the large number of participants moving through the measurement stations which could potentially cause errors in measurement recording if the study ID was the only identifier. These forms will be transported from the study site in a locked briefcase and will be kept in a locked file cabinet at the USDA Human Nutrition Research Center on Aging, as detailed in the confidentiality section below.

All study participants will be provided with pedometers (Yamax Digiwalker CW-701) to self-monitor their activity for one week at baseline, month 6, month 12 and month 18. Pedometers will be distributed and collected by study staff members at the beginning and end of each of these time points, and will be retained by the study staff at the end of the study. When pedometers are provided it will be emphasized that care and return are critical, however if they are lost there will be no penalty or replacement. Furthermore, they will be asked to self-report their activity for a week at baseline, month 6, month 12, and month 18 using the StudyTRAX database with electronic data capture that is built in to protect data confidentiality.

**Dietary Recalls:** Adherence to the energy intake and specific dietary recommendations of each intervention will be determined with 2 random 24 hour recalls by phone at three time points (baseline, during month 6 (active weight loss) and during month 18 (weight maintenance)), for a total of 6, 24 hour recalls throughout the entire study period. The recalls will be collected and analyzed by the Dietary Assessment Unit at Tufts, which provides a centralized and high standard dietary data service. The recalls will be analyzed for energy intake, macronutrient distribution, total fiber, energy density and meal patterns using Nutrition Data System for Research software version, 2012 developed by the Nutrition Coordinating Center (NCC), University of Minnesota, Minneapolis, MN. We have considerable experience with dietary records of different kinds and a history of lower underreporting than is typical (65). In addition, we will screen our dietary data prior to statistical analyses to eliminate implausible records (66, 67).

**Provided Foods:** Participants in the diet arm receiving the provided Yevo foods, will also be asked to check the log for meals consumed each day and record reasons for not consuming each meal such as satiety, monotony, palatability etc. Participants will be supplied with these foods monthly at their worksite for the first six months (equivalent to 2 meals/day during the first 12 weeks, and 1 meal/day for the following 12 weeks). No meals will be provided after this period, however weight maintenance in participants randomized to receive the meal will be examined for over the 18 month study duration, along with follow-up surveys to gauge participant enjoyment and opinion of provided Yevo foods.

